### The qualitative study

A subsample of participants in both arms of the trial will be invited for in-depth semistructured interviews over the course of the intervention period. A sampling framework will be used that ensures participants are included that are representative of the sociodemographic characteristics and clinical profile. Interviews at baseline (T0) will focus on the experience of living with FCD and subsequent interviews (at T1), not necessarily with the same participants, will explore their views on the ACT intervention. These interviews will focus on the acceptability, number, and frequency of ACT sessions, ways of optimising engagement, perceived benefits/limitations of the intervention, and any recommendations for improvement of the components and/or content of the intervention.

Interview schedules will be coproduced by the patient and public involvement (PPI) representatives and the research team. One-to-one, in-depth interviews will be carried out via teams by the research assistant, recorded and transcribed, and the transcripts cross-checked against the original recordings to ensure accuracy. The analysis will be led by the qualitative study expert and research assistant using reflexive thematic analysis^38^ aided by NVivo V.12 software. The results of the T1 interviews will be used to optimise the intervention during the feasibility study with the aim of developing a formalised intervention to be used in a future RCT.

### Data management

All data will be inputted by the participants themselves on to the trial database on REDCap and backed up weekly on a secure server. The electronic Trial Master File will be backed up weekly on an additional encrypted hard drive. No paper copies will be stored. Please refer to data management plan (see online supplemental appendix 5), for details regarding confidentiality, data collection, data handling and data transfer. The data collection and management will be in line with GDPR Data Protection Act (2018) and SWLSTG’s Information Governance.

10.1136/bmjopen-2023-072366.supp5Supplementary data

### Patient and public involvement

The research design has been informed by our PPI representatives who were recruited from earlier pilots of the intervention conducted within the SWLSTG Neuropsychiatry Service. They assisted in the development of the intervention, study methodology and review of clinical outcome measures. Two PPI participants ([name]) have been recruited to the TSC and are funded to assist with reviewing study materials, writing and developing patient information leaflets, producing the semistructured interview schedules for the qualitative study, and ensuring proper conduct of the study. We will document PPI activity over the course of the study in order to accurately assess where and how the lived experience perspective has been used and its impact on the research process and findings. All PPI representatives have lived experience of FCD and the proposed ACT intervention.

### Serious adverse events

All AEs and SAEs reported spontaneously by participants or observed by researchers will be recorded and reported to the trail manager (TM) and chief investigator (CI). Urgent actions concerning participant and staff safety, communication with others and clinical care will be immediately addressed by the CI and reported to the TMG. A summary of (S)AEs will be presented at each TMG and TSC meeting. AEs will be categorised for severity and seriousness by the TM and CI. SAEs will be further reviewed for relatedness to trial procedures and unexpectedness by the CI initially, and additionally by the chair of the TSC.

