St George’s Hospital in South London, in collaboration with South West London and St George’s National Health Service Mental Health Trust, is a centre of excellence for functional neurological disorders. We have developed a five-session group treatment based on the third-wave CBT known as acceptance and commitment therapy (ACT). This intervention focuses on changing a person’s relationship with their thoughts and feelings. It makes use of mindfulness and acceptance processes and increases values-driven behaviour.^12^ ACT considers psychological inflexibility—behaviour that is driven by attempts to excessively control internal experiences (such as difficult thoughts and feelings)—as a source of emotional distress; hence, its aim is to enhance psychological flexibility.^13^ Psychological flexibility is defined as ‘the ability to contact the present moment more fully as a conscious human being, and to change or persist in behaviour when doing so serves valued ends’^14^ while psychological inflexibility is regarded a transdiagnostic process common to numerous psychopathological states.^15^

Perceived threat is thought to be a maintenance factor for FND. Symptoms, such as cognitive failures in the case of FCD, are experienced as threatening, which causes hypervigilance and autonomic arousal. Symptoms are, therefore, experienced in a ‘top-down’ manner—influenced by cognitive and neurobiological processes of expectations and predictions of illness.^5 16^ Improvement with ACT occurs through six key processes that can be grouped as either ‘mindfulness and acceptance processes’ or ‘commitment and behaviour change processes’.^12^ Consequently, ACT aims to change a person’s relationship with their internal experiences, increasing psychological flexibility and altering the top-down expectations by facilitating bottom-up processes, for example, enhancing connection with direct experiences through mindfulness practices.

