#### Service utilisation and other cost variables

The Adult Service Use Schedule (AD-SUS)^30^ is a self-report service use questionnaire completed by the study participant in an interview with a trained researcher. The AD-SUS was developed by the study economist for previous work in similar populations and has been adapted for the needs of this study so that participants can complete this without assistance.

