### The ACT intervention

The group consists of psychoeducation about normal memory functioning, including the roles of attention and normal patterns of forgetting. The psychoeducation element aims to reduce the threat of cognitive symptoms. In line with the ACT model, the aim is to increase psychological flexibility (our proposed primary clinical outcome measure for a future RCT; AAQ-II) in response to the symptoms and associated thoughts and feelings.

The concept of ‘secondary suffering’ is introduced.^32^ It is suggested that attempts to control cognitive ‘failures’ leads to additional suffering, such as ruminations, negative predictions and avoidance. It is explicitly stated that the intervention does not aim to reduce ‘primary suffering’ (the cognitive symptoms), although it is possible that improvements may occur if secondary suffering is reduced. Brief mindfulness practices are incorporated in the group to facilitate ‘bottom-up’ processing, acceptance and more neutral interpretations of unwanted experiences. Value-based goals are identified throughout the sessions in order to shift away from avoidance-based behaviour and the focus on cognitive symptoms.

Participants will be given the time of all ACT sessions prior to randomisation and are asked to consent only if able to attend should they be randomised to the active intervention. They will sent an email with link and diary invite for all the sessions the week before the first session and follow-up reminder calls/emails each week to maximise attendance and engagement despite their memory problems. If a participant fails to attend a session, they will receive a follow-up call from the research assistant to ensure they had the time and link and to enquire about future attendance.

The intervention protocol (see online supplemental appendix 4) will be amended in response to specific feedback received during the contemporaneous qualitative interviews which are designed to explore the participants experience of and satisfaction with the groups.

10.1136/bmjopen-2023-072366.supp4Supplementary data

The intervention group will also receive TAU, as below.

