### Treatment as usual

TAU was selected as the fairest comparison, given that is what most patients in the UK currently receive within mental health and cognitive neurology settings. It consists of an explanation of the FCD diagnosis, provision of additional information about the diagnosis and underlying factors (such as medications, chronic pain or poor sleep hygiene; information: https://www.neurosymptoms.org/en/symptoms/fnd-symptoms/functional-cognitive-symptoms), and signposting to local psychological services in primary care (IAPT) for appropriate treatment, such as CBT, when comorbid anxiety and/or depression have been identified. TAU will be delivered as part of routine clinical care by the recruiting service.

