### Ethics and dissemination

Ethics approval was sought from the South East Scotland Research Ethics Committee (REC) 02 and a favourable opinion was received on 30 September 2022 (REC reference: 22/SS/0059). Any amendments to the protocol will be agreed with the REC before being implemented and then amended on the ISCTRN Registry. The findings of the study will be published in an open-access journal once the full trial has been completed. A data monitoring committee was not deemed necessary as participants are adverse effects are not expected in either of the randomisation groups.

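### Adverse events are described as spontaneously reported or observed, but study contact differs by arm and Table 1 does not say how scheduled events are obtained, so AE counts by arm would be open to unequal ascertainment

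*Protocol article*

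**What the plan says.** **Capture of adverse events.** The section Serious adverse events of the Protocol article states: "All AEs and SAEs reported spontaneously by participants or observed by researchers will be recorded". It describes no standard question or checklist. Table 1 has an AEs/SAEs row marked at T0, T1, T2 and T3, with no distinction by arm and no method.

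**Contact in the ACT arm.** The Introduction says "We have developed a five-session group treatment". The section The ACT intervention adds "follow-up reminder calls/emails each week to maximise attendance and engagement despite their memory problems", and then: "If a participant fails to attend a session, they will receive a follow-up call from the research assistant".

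**Contact in the TAU arm.** The section Treatment as usual says "TAU will be delivered as part of routine clinical care by the recruiting service". No study sessions or calls are described for this arm.

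**Mode of assessment, both arms.** Data management says "All data will be inputted by the participants themselves on to the trial database on REDCap". The service-use questionnaire, originally an interview, was "adapted for the needs of this study so that participants can complete this without assistance". The weblink is stated explicitly for baseline, and paper is an option.

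**Use of the data.** AEs and SAEs are summarised for the trial management group (TMG) and trial steering committee (TSC), and cases are reviewed for severity, seriousness, relatedness and unexpectedness. Under Ethics and dissemination, "A data monitoring committee was not deemed necessary", because adverse effects are not expected in either arm.

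**The concern.** An event that must be volunteered or noticed needs an occasion for that to happen. The ACT arm has many such occasions by design and the TAU arm has few that the article describes. If the text is followed as written, two arms with the same true event rate could produce different counts, with ACT the higher.

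The participants also report memory failures, and the protocol sends the ACT arm weekly reminders for that reason. Unprompted recall of events is a weak basis for counting in this population.

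At stake is how the AE summary is read by the TMG and TSC, and by whoever plans the definitive trial. ACT could look less safe than it is, and a low TAU count could reflect silence rather than absence of events. Events that were never asked about cannot be recovered at analysis.

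**Working it through.** **1. Is there a figure to reproduce?** No. The article gives no AE rate, no capture rate and no safety contrast. The check is a comparison of sections, followed by an illustration on assumed figures.

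**2. The sections side by side.**

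| Item | ACT + TAU | TAU alone |
|---|---|---|
| Group sessions | five | none |
| Weekly reminder calls/emails | yes, around the sessions | none described |
| Call after a missed session | yes | not applicable |
| Routine care from the recruiting clinic | yes | yes |
| Questionnaires at T0 to T3 | largely self-completed | largely self-completed |
| AEs/SAEs row in Table 1 | T0 to T3, method not stated | T0 to T3, method not stated |

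The additional contact is all on the ACT side. Table 1 shows the intervention as completed by T1, so the imbalance falls mainly between T0 and T1.

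**3. Does Table 1 settle the method?** There are two readings. If the row means that everyone is asked the same question at each time point, the word spontaneously in the text is incomplete or wrong. If it means that whatever has been volunteered or observed is logged at those times, capture depends on contact. The article does not say which applies.

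**4. Illustration (assumed figures).** Recorded risk = true risk × probability of capture. Take a true risk of 20% in both arms, 24 participants per arm (from the section Sample size) and 90% capture in ACT.

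- ACT recorded risk: 0.20 × 0.90 = 0.18; expected count 24 × 0.18 = 4.3.
- Risk ratio (RR) = capture in ACT / capture in TAU; the true risk cancels.
- 95% half-width of the risk difference (RD) = 1.96 × √[p₁(1 − p₁)/24 + p₂(1 − p₂)/24].

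| TAU capture (assumed) | Recorded, ACT v TAU | Expected counts | RR | RD (points) | 95% half-width (points) |
|---|---|---|---|---|---|
| 90% | 18% v 18% | 4.3 v 4.3 | 1.00 | 0 | 21.7 |
| 70% | 18% v 14% | 4.3 v 3.4 | 1.29 | 4 | 20.7 |
| 50% | 18% v 10% | 4.3 v 2.4 | 1.80 | 8 | 19.5 |
| 30% | 18% v 6% | 4.3 v 1.4 | 3.00 | 12 | 18.1 |

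The same ratios arise at a true risk of 10% or 30%. In every row the sampling half-width exceeds the spurious difference.

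**The case against.** The strongest reply is that the document plans nothing for this bias to damage. A reader might infer that a between-arm safety comparison is biased, but the Statistical analysis plan section contains no AE analysis by arm, and safety is not among the four primary outcomes and progression criteria. That stands. The point concerns counts that may be shown by arm, not a stated analysis.

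A reader might also infer that AEs are recorded only if volunteered or observed. The text does not say only, and the Table 1 row fits a common question as well as passive logging. The full protocol and appendices, which are not shown, may describe one. This stands as far as it goes, but an elicited question would still leave the published description needing correction.

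A third tempting reading is that deterioration in TAU participants or ACT non-attenders would go unseen. Table 1 does not support it. PHQ-9 and GAD-7 at T0 to T3, and the service-use schedule at T0 and T3, pick up some worsening and service use in both arms on the same timetable. ACT participants who miss a session are telephoned. What could be missed is an event as an AE record, not all worsening.

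Nor does the document show that TAU participants have no live contact. They are told their allocation, they are seen by a clinical service, and some may be interviewed. Part of the ACT contact is email.

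Finally, the illustrated ratios simply restate the assumed capture rates, and the counts are too small to support a safety conclusion either way. Both remarks are correct. The direction does not depend on the assumed figures, but the size does.

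**Conclusion.** The point holds in a limited form. The text describes capture by spontaneous report or observation, Table 1 schedules AEs/SAEs at four common time points without a method, and the ACT arm has more study contact. Under the text as written, AE counts by arm would be subject to unequal ascertainment, most likely inflating ACT relative to TAU.

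The size cannot be derived from the document. An RR of 1.29 to 3.00 under equal true risk rests wholly on assumed capture of 90% in ACT against 70% to 30% in TAU. If the Table 1 row already means equal questioning of both arms, the ratio is 1.00 and only the wording needs correcting.

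Severity is minor to moderate: a change worth considering in a 48-person feasibility study with safety outside its progression criteria.

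**What to change.** - Put one structured AE question, worded identically for both arms, on the existing T1, T2 and T3 forms.
- In any AE table by arm, show these solicited events separately from those reported spontaneously or observed. Otherwise the extra ACT contact would re-enter the count even with a common question.
- Amend Serious adverse events so that it agrees with the AEs/SAEs row of Table 1, stating how events are obtained at each time point. If a common question is already asked, this sentence and the separate tabulation are all that is needed.
- Where counts are shown by arm, note that spontaneous and observed events reflect unequal contact.

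The cost is one form item and a sentence or two of text. The downside is slightly longer questionnaires and more minor events to log and categorise.

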### Ethics and dissemination

Ethics approval was sought from the South East Scotland Research Ethics Committee (REC) 02 and a favourable opinion was received on 30 September 2022 (REC reference: 22/SS/0059). Any amendments to the protocol will be agreed with the REC before being implemented and then amended on the ISCTRN Registry. The findings of the study will be published in an open-access journal once the full trial has been completed. A data monitoring committee was not deemed necessary as participants are adverse effects are not expected in either of the randomisation groups.
